| **Maximum Tolerated Dose (MTD)** | The maximum tolerated dose (MTD) refers to the lower dosage next to a dose with which DLT occurs in 2 or more out of 6 patients during the DLT evaluation window. |
| **Dose-Escalation Phase** | The doses are proposed to be escalated to 0.1 mg/kg, 0.5 mg/kg, 1.0 mg/kg, 1.5 mg/kg, 2.0 mg/kg, 2.5 mg/kg, 3.0 mg/kg, 3.5 mg/kg and 4.0 mg/kg (if the last dose has not yet reached the MTD, it should continue to increase by 0.5 mg/kg).  On Oct. 18, 2016, the investigators and sponsor decided to add a dose-escalation trial with Q3W administration in the dose-escalation phase. Starting from the 2.0 mg/kg dose group, 2-3 patients are enrolled. Pharmacokinetic data from Q3W administration are collected repeatedly. The dose next to 2.0 mg/kg is determined based on the results of the dose escalation study with Q2W administration. The extended trial is started with the 2.0 mg/kg dose group.  On July 4, 2017, the investigators and sponsor decided that: 1) Symptomatic treatment is allowed during the DLT evaluation period. Dose escalation trials are performed in subjects according to the traditional 3+3 mode, wherein doses are proposed to be escalated from 2.5 mg/kg to 3.0 mg/kg, 3.5 mg/kg and 4.0 mg/kg with Q2W administration until MTD is reached, or the sponsor and investigators decide to terminate the escalation study. 2) The original dose-escalation study starting with 2.0 mg/kg Q3W is stopped. Dose escalation trial is carried out with an initial dose of 1.25mg/kg, followed by 1.5mg/kg, in the traditional 3+3 mode with QW administration. Symptomatic supportive treatment is allowed in the DLT evaluation period until MTD is reached. If the 1.5 mg/kg dose group does not reach MTD, the sponsor and investigators will jointly decide on the next escalating doses or whether to terminate the dose escalation trial. |

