If DLT appears in the subjects, treatment of RC48-ADC should be discontinued first, and adverse reactions should be dealt with actively until the toxicity returns to ≤ Grade 1. Thereafter, medication should proceed at a decreased dose level (specific doses will be determined by the investigators).

**Maximum Tolerated Dose (MTD)**: The lower dosage next to a dose with which DLT occurs in 2 or more out of 6 patients during the DLT evaluation window.

Dose groups of 3 to 6 subjects were formed starting with the lowest dose set by the protocol:

(1) If none of the 3 subjects develop DLT within the 21-day observation period after the first dose, the next (escalated) dose trial can be performed.

(2) If DLT occurs in 1 of the 3 subjects, the number of subjects in this dose group should be increased to 6: (a) if DLT occurs in 2 or more of these 6 subjects, the next (escalated) dose trial should be terminated; (b) if DLT occurrs in no more than 1 of the 6 patients, the next (escalated) dose trial can be performed.

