**On July 4, 2017, the investigators and sponsor decided to modify the DLT definition based on the current study results:**

**DLT** refers to the following toxic reactions observed in the DLT evaluation window (observation period of Day 1-21 after the first dose) that are considered related to RC48-ADC treatment by the investigators or sponsor, wherein the grading is based on the 5-level system of the CTCAE v4.0:

- Grade 4 neutropenia lasting more than 3 days after symptomatic treatment; or grade 4 neutropenia recurring after recovery to a normal level through symptomatic treatment.
- Neutropenic fever (defined as absolute neutrophil count ^[^ANC] < 1000/mm3 accompanied by a fever higher than 38.3 °C or a fever above 38 °C that persists for more than 1 h).
- Grade 3 neutropenia with confirmed infections.
- Grade 3 thrombocytopenia with bleeding tendency.
- Grade 4 thrombocytopenia.
- Non-hematologic toxicity of Grade 3 or higher after supportive care. Except for nausea, vomiting and hair loss.
- Renal toxicity ≥ Grade 3.
- Neurological toxicities ≥ Level 2 that persist until the next administration.
- Cardiac toxicity ≥ Grade 2.
- Hepatic transaminases reach grade 2 at baseline, with a level ≥10×ULN.

If DLT appears in the subjects, treatment of RC48-ADC should be discontinued first, and adverse reactions should be dealt with actively until the toxicity returns to ≤ Grade 1. Thereafter, medication should proceed at a decreased dose level (specific doses will be determined by the investigators).

**Maximum Tolerated Dose (MTD)**: The lower dosage next to a dose with which DLT occurs in 2 or more out of 6 patients during the DLT evaluation window.

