**Blood Collection for PK During Dose-Escalation Trial:**

Blood collection time points for Q2W administration:

The blood collection points for the first dose (11 blood collection points): before administration (0 h), 0.25 h, at the end of infusion, 1.5 h, 12 h, 24 h, 48 h, 72 h, 120 h, 168 h and 240 h.

For the second dose (1 blood collection point): before administration (336 h).

For the third dose (1 blood collection point): before administration (672 h).

For the fourth dose (12 blood collection points): before administration (1008 h), 0.25 h (1008.25 h), at the end of infusion, 1.5 h (1009.5 h), 12 h (1020 h), 24 h (1032 h), 48 h (1056 h), 72 h (1080 h), 120 h (1128 h), 168 h (1176 h), 240 h (1248 h) and 336 h (1344 h).

Blood samples are collected at these 25 time points to detect serum ADC, TAb and free MMAE, with a collection volume of 2 mL each time.

Blood collection points for immunogenicity (ADA) assays: Serum anti-ADC antibodies are detected before the first, second, third and fourth doses, and 336 hours after the fourth dose (5 collection points), with 1 mL of blood volume for each sample.

Blood collection time points for Q3W administration:

The blood collection points for the first dose (11 blood collection points): before administration (0 h), 0.25 h, at the end of infusion, 1.5 h, 12 h, 24 h, 48 h, 72 h, 120 h, 168 h and 240 h.

For the second dose (1 blood collection point): before administration (504 h).

For the third dose (12 blood collection points): before administration (1008 h), 0.25 h (1008.25 h), at the end of infusion, 1.5 h (1009.5 h), 12 h (1020 h), 24 h (1032 h), 48 h (1056 h), 72 h (1080 h), 120 h (1128 h), 168 h (1176 h), 336 h (1344 h) and 504 h (1512 h).

Blood samples are collected at these 24 time points to detect serum ADC, TAb and free MMAE, with a collection volume of 2 mL each time.

Blood collection points for immunogenicity (ADA) assays: Serum anti-ADC antibodies were detected before the first, second and third doses, and 504 h after the third dose (4 collection points), with 1 mL of blood volume for each sample.

Blood collection time points for QW administration:

The blood collection points for the first dose (9 blood collection points): before administration (0 h), 0.25 h, at the end of infusion, 1.5 h, 12 h, 24 h, 48 h, 72 h and 120 h.

For the second dose (1 blood collection point): before administration (168 h).

For the third dose (1 blood collection point): before administration (336 h).

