If there occurs a QTcF interval > 500 ms or increasing by > 60 ms relative of the baseline or grade III atrioventricular block during trial, then the trial medication should be suspended. The investigators will decide whether or not to continue medication after defining its cause.

In a non-DLT observation cycle, if any clinically significant AE occurring in one subject is judged by the investigators to be potentially, probably or definitely relevant to the study drug, and this AE is likely to continue or be potentially aggravated in the next scheduled dosing, then the investigators may postpone dosing or stop one dose of the study drug, the delay may last for up to 21 days or dose level may be lowered by 1 or 2.

The following provisions apply to toxic reaction occurring beyond DLT evaluation window.

Non-Hematological Toxicity

If any grade 4 non-hematological toxicity occurs in a patient postdose, or there occurs any important injury of organs such as lungs, cardiovascular system, liver and kidneys, then treatment of the patient should be immediately terminated.

If a patient gets any clinical benefit after treatment, but exhibits over grade 3 non-hematological toxicity (except hair loss, nausea, and emesis) and can be recovered to normal, grade 1 or baseline level in 14 days after the optimal supportive therapy, then one dose reduction is allowed. The specific dose shall be determined by the investigators and the sponsor through mutual negotiation (it may be a previous dose subjected to safety assessment or an arbitrary dose previously assessed). If the subject fails to be recovered to normal, grade 1 or baseline level in 14 days, then the investigators and the sponsor will discuss and decide whether or not to terminate the study treatment. If a toxic reaction occurs at the first dose level, then the dose can be reduced to 50%. Subsequent dose escalation trial will be adjusted by the investigators and the sponsor through negotiation.

Hematological Toxicity

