## 10.2 Drugs may be Conditionally Used During Study

When non-DLT adverse events occur during the DLT observation period of the dose escalation phase, no medical treatment (including but not limited to dosing suspension and symptomatic treatment) should be provided in principle in order to observe possible adverse reactions (including severity and reversibility) to the investigational drug. Once any DLT toxic reactions specified in the protocol occur, medication must be discontinued immediately and active treatment must be provided. Medications should be recorded on CRF. Adverse events occurring during the non-DLT observation period should be dealt according to "(8) Safety and Tolerability Evaluation" of outcome measures described in Protocol 7.

On July 4, 2017, the investigators and sponsor determined that during the dose escalation phase starting with 2.5 mg/kg Q2W and dose-escalation trial with an initial dose of 1.25 mg/kg QW, adverse events occurred within the DLT observation period may be dealt with symptomatic treatments as necessary upon investigators' judgment; G-CSF treatment is allowed for Grade 4 neutropenia but prohibited for preventive application. Once any DLT toxic reactions specified in the protocol occur, medication must be discontinued immediately and active treatment must be provided. Medications should be recorded on CRF.

In principle, medication should not be discontinued when a subject experiences a toxic reaction during the extended trial. Doctors may administer appropriate treatment according to the specific situation based on the following principles:

Doses are escalated in an order of 2 mg/kg, 1.5 mg/kg, 1 mg/kg and 0.5 mg/kg, with 0.5 mg/kg as the lowest dose.

Myelosuppression: In case of myelosuppression, investigators may perform symptomatic treatments based on clinical manifestations. If Grade III or higher neutropenia occurs, GSF treatment should be provided. Specific dose modification is shown in Table 5.

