- Grade 4 thrombocytopenia.
- Non-hematologic toxicity of Grade 3 or higher after supportive care. Except for nausea, vomiting and hair loss.
- Renal toxicity ≥ Grade 3.
- Neurological toxicities ≥ Level 2 that persist until the next administration.
- Cardiac toxicity ≥ Grade 2.
- Hepatic transaminases reach grade 2 at baseline, with a level ≥10×ULN.

(3) On July 4, 2017, the investigators and sponsor decided to let 3-5 study sites participate in the extended trial phase based on the current study results. At least 10 patients with HER2 ICH 2+/FISH- and at least 20 patients with HER ICH 2+/FISH+ or ICH 3+ with advanced solid tumors (gastric cancer is preferable) are enrolled and administered at 2.0 mg/kg Q2W until disease progression or intolerable adverse reactions.

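### The general non-hematologic DLT item lets supportive care excuse Grade 4 as well as Grade 3, so a related Grade 4 event that care controls need not enter the 3+3 count

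*Protocol*

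**What the plan says.** The DLT list in force since July 4, 2017 appears in the Study Summary, in Section 3 and in Section 18. All three carry the same general item: "Non-hematologic toxicity of Grade 3 or higher after supportive care. Except for nausea, vomiting and hair loss". The list that preceded it has the same wording. The only time limit is the Day 1-21 window.

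Other items in the current list are tighter. Grade 4 neutropenia must last more than three days after treatment or recur. Neurotoxicity is read at the next dose. Renal toxicity of Grade 3 or higher and cardiac toxicity of Grade 2 or higher count with no reference to care.

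Section 10.2 gives the treatment rules for the window. For events that were not DLTs, the older rule was that "no medical treatment (including but not limited to dosing suspension and symptomatic treatment) should be provided in principle". Since July 4, 2017, for Q2W escalation from 2.5 mg/kg and for QW escalation, "adverse events occurred within the DLT observation period may be dealt with symptomatic treatments as necessary". The Study Summary agrees: "Symptomatic treatment is allowed during the DLT evaluation period".

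Escalation depends on the DLT count alone. Section 3 allows the next dose "If none of the 3 subjects develop DLT within the 21-day observation period after the first dose". One DLT in three adds three subjects, and two or more in six stops escalation and puts the MTD one level lower.

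**The concern.** A Grade 4 event is life-threatening or needs urgent intervention, and excusing it because treatment worked is a different matter from excusing a manageable Grade 3 event. The general item makes no such distinction. While events in the window were in principle left untreated, the qualifier had little room to act. Now that care is allowed in the window, it can decide whether an event counts.

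The DLT count fixes the MTD, which is a primary objective. A single event left out turns 1 of 3 into 0 of 3 (escalate instead of expand), or 2 of 6 into 1 of 6 (escalate instead of stop). The events exposed are those outside the named organ items, for example diarrhea, rash, infusion reactions and pulmonary or metabolic toxicity.

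**Working it through.** **Text check: does any other rule put such an event into the DLT count?**

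- Section 7 (8) ends treatment at once in this case: "If any grade 4 non-hematological toxicity occurs in a patient postdose, or there occurs any important injury of organs such as lungs". Its lead-in limits these provisions to toxicity beyond the DLT window, and they concern the patient's treatment, not the DLT count.
- Section 5 permanently stops drug after a life-threatening infusion reaction. Section 11.1 classes life-threatening events as SAEs and stops drug. Neither adds a DLT.
- Table 8 discontinues drug at a first Grade IV event among other toxicities, but it belongs to the extended trial.
- Sponsor and investigators may end escalation at their discretion. That is permission, not a rule.

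So none does. Elsewhere the protocol treats Grade 4 as decisive; the general DLT item does not.

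**Illustration of size.** The protocol gives no target DLT rate and no rate for these events, so both inputs are assumptions:

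- d = per-subject rate of all other DLTs: 10% or 20%.
- g = per-subject rate of related Grade 4 events under the general item that care brings below Grade 3: 2%, 5% or 10%.
- The two are taken as independent. Not counted: p = d. Counted: p = 1 − (1 − d)(1 − g).

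From the 3+3 rule in Section 3:

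- P(clear) = (1 − p)³ + 3p(1 − p)² × (1 − p)³
- P(expand to 6) = 3p(1 − p)²
- P(first-cohort decision changes) = (1 − d)³[1 − (1 − g)³] + 3d(1 − d)²[1 − (1 − g)²]. The first term is a cohort at 0 of 3 moved to 1 or more. The second is a cohort at 1 of 3 moved to 2 or more.

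Worked case, d = 10% and g = 5%: p = 1 − 0.90 × 0.95 = 0.145. P(clear) not counted = 0.729 + 0.243 × 0.729 = 0.906. P(clear) counted = 0.625 + 0.318 × 0.625 = 0.824. Decision change = 0.729 × 0.1426 + 0.243 × 0.0975 = 0.128.

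| d | g | p if counted | Clear, not counted | Clear, counted | Fall (points) | First-cohort decision changes | Expand, not counted → counted |
|---|---|---|---|---|---|---|---|
| 10% | 2% | 0.118 | 0.906 | 0.875 | 3.1 | 5% | 24% → 28% |
| 10% | 5% | 0.145 | 0.906 | 0.824 | 8.2 | 13% | 24% → 32% |
| 10% | 10% | 0.190 | 0.906 | 0.730 | 17.6 | 24% | 24% → 37% |
| 20% | 2% | 0.216 | 0.709 | 0.674 | 3.5 | 5% | 38% → 40% |
| 20% | 5% | 0.240 | 0.709 | 0.622 | 8.7 | 11% | 38% → 42% |
| 20% | 10% | 0.280 | 0.709 | 0.536 | 17.3 | 21% | 38% → 44% |

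**Where g may lie.** Section 1.5 reports 25 subjects at doses up to 2.5 mg/kg and names no such event, though it is not a full event list. Read as 0 of 25, the one-sided 95% upper limit is 1 − 0.05^(1/25) = 11.3%. So g = 10% is near the top of what those data allow. Nothing is known for 3.0 to 4.0 mg/kg.

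**The case against.** The best counter-argument is that the list counts toxicities observed in the window, so an event still at Grade 3 or higher at any moment after care begins already meets the item. Section 3 then describes treating a DLT until it falls to Grade 1 or below, so recovery does not cancel one. Section 10.2 requires drug to stop immediately once a DLT occurs, which fits badly with waiting to see where the grade settles. These points make the strict reading reasonable. But those sentences say what follows once an event is a DLT; they do not settle whether this event is one. The qualifier still allows the lenient reading.

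It is also fair that the July 2017 revision changed the neutropenia item and left this one, that the affected pool is small, and that every rate above is assumed.

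A reader might go further than the documents allow in three ways:

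- **Sites will score the same event differently.** The 3-5 sites are added for the extended phase, at a fixed 2.0 mg/kg Q2W, where DLTs drive no escalation. Nothing assigns escalation cohorts to them.
- **Such a patient would go on being dosed while the grade is awaited.** The window does hold later doses; on QW the protocol has "For the second dose (1 blood collection point): before administration (168 h") and another at 336 h. But a life-threatening event is an SAE, which stops drug and is reported within 24 hours. Further dosing is unlikely.
- **Every cohort with such an event is affected.** At least one event occurs in 6%, 14% or 27% of three-subject cohorts, from 1 − (1 − g)³. In some of them the subject already has another DLT or the cohort is already at two or more, so fewer decisions change.

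The absence of a fixed reading time for Grade 3 is mostly missing detail and does not carry the point.

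**Conclusion.** The point holds for the general non-hematologic item only. As written, a related Grade 4 event that care brings below Grade 3 need not be a DLT, and no other rule puts it into the count. The patient is protected by other rules, but the escalation decision is not.

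Under the assumed rates, counting such events lowers the chance of clearing a dose by about 3 points (g = 2%), 8-9 points (g = 5%) or 17-18 points (g = 10%). The low end is more likely at doses up to 2.5 mg/kg. The figures compare the lenient reading with counting all such events, assume independence from other DLTs, and leave out Grade 3 events. The documents do not show that any dose has been cleared wrongly, or that the July 2017 revision introduced the wording, which is older. This is an inexpensive improvement to the rule, not a defect that undermines the trial.

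**What to change.** In the three current lists (Study Summary, Section 3, Section 18):

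1. State that any related Grade 4 or higher toxicity under the general non-hematologic item with onset in Day 1-21 is a DLT regardless of supportive care. Keep the exceptions for nausea, vomiting and hair loss, and exclude asymptomatic laboratory abnormalities corrected within a time that the amendment states.
2. Keep the supportive-care qualifier for Grade 3 only, and read the remaining grade no later than the next scheduled dose, as the neurotoxicity item does. Where that dose falls after Day 21, say in the 3+3 text that the event belongs to the window by its onset day.
3. At each escalation decision, show related Grade 3 or higher non-hematologic events by worst grade beside the DLT count.

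The renal, cardiac, neurologic and transaminase items stay as they are. The cost is amendment wording and one column in the cohort review. The downside is more expansions (last column of the table) and possibly a lower MTD. Group size stays within the 3-6 of Table 1.

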Subjects are enrolled in the traditional 3+3 mode from the third dose (1.0 mg/kg) forward. At first, 3 qualified subjects are enrolled into the 1.0 mg/kg group. If no DLT is observed in the 3 subjects during the DLT evaluation period, the dose is escalated to the next level; if DLT occurs in 1/3 of the subjects (1 case) in the 1.0 mg/kg group, another 3 subjects should be added. If no DLT is observed in the additional 3 subjects, trials at the next dose level may be started; if DLT occurs in 1 or more of the 3 additional subjects, or in 2 or more of the 6 subjects in total, the dose escalation should be discontinued. Trials in the same manner are performed with dose escalation until the maximum tolerated dose (MTD) and recommended phase Ⅱ dose (RP2D) are determined.

[figure not shown]

All subjects are evaluated as CR, PR or SD after the 4th administration. If the patients are willing to do so, and the investigator determines that continued administration will be of benefit to the patients, patients can enter the extended test in which treatment is continued until the disease progresses, the toxicity become intolerable, the patients withdraw consent or the investigator determines that the medication must be discontinued.

**Dose-limiting toxicity (DLT)** refers to the following toxic reactions observed in the DLT evaluation window (observation period of Day 1-21 after the first dose) that are considered related to RC48-ADC treatment by the investigators or sponsor, wherein the grading is based on the 5-level system of the CTCAE v4.0:

- Grade 4 neutropenia.
- Neutropenic fever (defined as absolute neutrophil count ^[^ANC] < 1000/mm3 accompanied by a fever higher than 38.3 °C or a fever above 38 °C that persists for more than 1 h).
- Grade 3 neutropenia with confirmed infections.
- Grade 3 thrombocytopenia with bleeding tendency.
- Grade 4 thrombocytopenia.
- Non-hematologic toxicity of Grade 3 or higher after supportive care. Except for nausea, vomiting and hair loss.
- Renal toxicity ≥ Grade 3.
- Neurological toxicities ≥ Level 2 that persist until the next administration.
- Cardiac toxicity ≥ Grade 2.
- Hepatic transaminases reach grade 2 at baseline, with a level ≥10×ULN.

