For the fourth dose (10 blood collection points): before administration (504 h), 0.25 h (504.25 h), at the end of infusion, 1.5 h (505.5 h), 12 h (516 h), 24 h (528 h), 48 h (552 h), 72 h (576 h), 120 h (624 h) and 168 h (672 h).

Blood collection points for immunogenicity (ADA) assays: Serum anti-ADC antibodies are detected before the first, second, third and fourth doses, and 336 hours after the fourth dose (5 collection points), with 1 mL of blood volume for each sample.

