# At baseline, all patients with solid tumors must undergo CT/MRI scans of the chest, abdomen and pelvis according to the RECIST v1.1. For osteopathy patients, confirmatory bone scan shall be carried out at the time of baseline. Tumor assessment will be performed by using CT/MRI/radiography. For subjects rated as CR or PR at the initial evaluation, their efficacy should be verified 4 weeks later. 1 evaluation should be performed every 2 cycles.

☆ ECG is required before each dose.

Note: Each treatment cycle includes 2 doses, and the efficacy should be evaluated every 2 treatment cycles.

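### Under Q2W escalation, a persisting Grade 2 neurotoxicity that starts after the Day 15 dose cannot be classified as a DLT until about Day 29, yet the protocol permits escalation once the Day 1-21 window closes

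*Protocol*

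**What the plan says.** The DLT window is Day 1-21 after the first dose (Protocol, Study Summary; Section 3 Study Design; Section 18 Content Added During the Trial). Among the DLTs, Section 3 lists "Neurological toxicities ≥ Level 2 that persist until the next administration". The item is the same in the initial definition and in the one adopted on July 4, 2017, and Section 18 repeats it. The Study Summary words it differently, as neurotoxicity of Grade 2 or higher that has not responded by the next dose.

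Two places in Section 3 govern clearance on 0 of 3. The cohort description says "If no DLT is observed in the 3 subjects during the DLT evaluation period, the dose is escalated to the next level". The numbered rules say "If none of the 3 subjects develop DLT within the 21-day observation period after the first dose", then "the next (escalated) dose trial can be performed". After expansion to 6 subjects, at most 1 DLT also clears the level, in permissive wording. The MTD is the level below one at which "DLT occurs in 2 or more out of 6 patients during the DLT evaluation window".

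Section 6 puts the second Q2W dose at 336 h and gives the third as "For the third dose (1 blood collection point): before administration (672 h". Appendix 2 notes "Each treatment cycle includes 2 doses", so the third dose is Day 1 of Cycle 2, with a visit window of ±1 day. The QW schedule has "For the fourth dose (10 blood collection points): before administration (504 h". Section 18 plans further Q2W escalation from 2.5 mg/kg to 3.0, 3.5 and 4.0 mg/kg.

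**The concern.** The neurotoxicity item depends on the patient's status at the next dose. For some onsets inside the window, that dose comes after the window has closed. The cohort rules look only at DLTs within the window and say nothing about an event that is present on Day 21 but cannot yet be classified.

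In a 3+3 design single events decide. One late-confirmed event turns 0/3 into 1/3, which means expanding to 6 instead of escalating. It turns 1/6 into 2/6, which means stopping instead of escalating. If the next level has opened in the meantime, patients have received a dose that the fully informed rule would have withheld.

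Neurotoxicity is a plausible toxicity here. Section 11.3 names peripheral sensory neuropathy as an expected effect of MMAE. Section 1.5 lists numbness among the drug-related events (6%), and numbness of hands and feet among the events that led to medication changes.

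**Working it through.** **Inputs.** Window: Day 1-21 (Section 3). Dose times in hours from the first dose: Q2W 0, 336, 672; QW 0, 168, 336, 504 (Section 6). Visit window for Cycle 2 Day 1: ±1 day (Appendix 2).

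**Step 1: dose days.** Day label = hours/24 + 1.
- Q2W: 0/24 + 1 = 1; 336/24 + 1 = 15; 672/24 + 1 = 29. This matches 14-day dosing.
- QW: Days 1, 8, 15, 22.
- The window ends at the close of Day 21, which is 21 × 24 = 504 h.

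**Step 2: which onsets can be judged in the window.** Under Q2W, an onset before the Day 15 dose is judged at that dose, inside the window. An onset after that dose and by Day 21 (7 of the 21 day labels) has Day 29 as its next dose. If it resolves earlier it can be ruled out earlier; if it persists, it can be confirmed only at Day 29.

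**Step 3: size of the gap.**
- Q2W elapsed time: 672 − 504 = 168 h = 7 days.
- Q2W by day label: 29 − 21 = 8. The labels differ by one more than the elapsed time because Day 21 ends where Day 22 begins.
- With ±1 day: 6 to 8 days elapsed, or 7 to 9 by label.
- QW: 504 − 504 = 0 h, or 22 − 21 = 1 by label.
- Day 29 is not an upper limit. Outside the DLT period, Sections 7 and 9 allow dosing to be postponed for a related event by up to 21 days, so the third dose could fall as late as Day 29 + 21 = 50.

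**Step 4: which grades.** Grade 3 or higher neurotoxicity falls under the general non-hematologic item, which is conditional on supportive care but not on the next dose. The wait for the next dose therefore matters for Grade 2.

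**Step 5: how many patients can be open.** At the earliest decision the last patient is at Day 21, and a patient first dosed d days earlier is at Day 21 + d. That patient is still before the third dose if 21 + d < 29, so d ≤ 7. Between 1 and 3 patients in a cohort of 3 can be in the gap.

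**Step 6: illustration on assumed rates.** The protocol gives no rate. If q is the chance per patient of an open event of this kind, the chance of at least one at the decision is q with one patient in the gap and 1 − (1 − q)³ with three.

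| q (assumed) | one patient | three patients |
| --- | --- | --- |
| 0.02 | 0.02 | 0.059 |
| 0.05 | 0.05 | 0.143 |
| 0.10 | 0.10 | 0.271 |

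These are chances of an open event. The chance of an unclassified true DLT is lower, because not every open event persists.

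**Step 7: steps affected.** The planned Q2W levels 2.5, 3.0, 3.5 and 4.0 mg/kg give three steps: 2.5 to 3.0, 3.0 to 3.5 and 3.5 to 4.0. At 4.0 only the MTD count is affected, unless escalation continues by 0.5 mg/kg as the Study Summary allows.

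**The case against.** The strongest reply is that the text mostly permits escalation and does not compel it. The numbered rules in Section 3 and the wording for the expanded cohort are permissive. Only the 0-of-3 sentence in the cohort description reads as an instruction. Section 3 also lets investigators and sponsor adjust increments on actual results, and Section 9 keeps subjects in hospital during PK collection, which under Q2W runs to 1344 h. An open event would be seen, and a careful team could wait. This stands as mitigation, but nothing obliges anyone to wait.

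A reader might infer that a late-confirmed event drops out of the MTD count. The documents do not support that as the likely reading. A DLT is defined as a reaction observed in the window, and persistence qualifies that reaction, so counting by onset is natural. The strict reading is not excluded, but the main harm is treatment at the next level too early, with the MTD count probably preserved.

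A reader might also infer that such events have already been missed. Section 1.5 gives no grade or onset for the numbness, and it reports that all symptoms resolved after dose discontinuation or symptomatic treatment. Section 10.2 now allows symptomatic treatment during DLT observation. No documented case fits the gap.

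Finally, other DLT items can need follow-up past Day 21, such as Grade 4 neutropenia lasting more than 3 days after treatment. That is true, and a general hold rule could cover them too. It does not answer the neurotoxicity item, whose wait is set by the dosing calendar.

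**Conclusion.** The point holds, within limits. As written, the protocol permits Q2W escalation about a week before a persisting Grade 2 neurotoxicity with onset after the Day 15 dose can be classified: 168 h = 7 days elapsed, Day 21 to Day 29 by label, ±1 day for the visit, and longer if the dose is delayed. It concerns related Grade 2 events only and three planned escalation steps. Under QW the timing fits to within one day label.

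The calendar result rests on the nominal dose times and on a window closing at the end of Day 21. How often it would matter cannot be derived from the document, and the percentages above are assumptions. The change is worth making because one event reverses either clearing outcome, and because the wording, if followed, can move patients to a higher dose over an event that the protocol itself lists as dose-limiting.

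**What to change.** In the DLT definitions of the Study Summary, Section 3 and Section 18, use one common wording for the item and state that:

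- a Grade 2 or higher neurotoxicity with onset on Days 1-21 is assessed on the date of the next scheduled dose, whether or not that dose is given, and is a DLT if it is still Grade 2 or higher on that date;
- such an event counts by its onset toward the cohort and MTD rules;
- if such an event is open on Day 21, the cohort decision is held until it resolves to Grade 1 or lower or is classified.

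In the MTD definition (Study Summary and Section 3), say that the DLT has its onset during the evaluation window. Using the scheduled date removes the dependence on a postponed dose.

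The cost is protocol wording and an occasional delay of about 7-8 days (up to 9 with the visit window) under Q2W, or at most one day label under QW, and only when such an event is open on Day 21.
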